## Abstract

**Background::**

Preschooler inactivity and insufficient motor development have serious long-term consequences. The Chinese Ministry of Education launched a nationwide football-focused pilot project aimed at kindergartens in 2019 and issued the policy “Notice on the Establishment of National Football Kindergartens” in 2020. However, the impact of fundamental movement skills (FMS) interventions on other aspects of child development is unclear.

**Aim::**

This study will evaluate the effects of ball skills physical education projects on the development of Chinese preschoolers’ physical, motor, cognitive, and social competencies and examine the influencing factors.

**Method::**

This is a quasi-experimental study evaluating how well the “Hello Sunshine” curriculum project promotes children’s development over 10 weeks. The trial will be conducted from September 2021 to November 2021 in 12 classes from 3 kindergartens with a total of 249 children aged 4 to 6 years in Haikou, China. Pre- and posttest analyses will include tests on participants’ physical fitness, FMS, cognitive self-regulation, and emotional competence. Participants’ background information will be collected through questionnaires answered by parents and teachers. The intervention will focus on game-based basic ball skills.

**Findings::**

If this intervention provides evidence that these skills improve children’s multidimensional development, it will support the promotion of similar programs in China. We will also outline the social-ecological factors affecting the intervention’s results, providing further information for improving pedagogical methods related to preschool ball skills.

## Introduction

The preschool years form an important stage in the development of children’s physical, motor, socioemotional, and cognitive skills (Chinese Ministry of Education, 2012; Leppänen *et al.*, 2016; Van Capelle *et al.*, 2017; Zeng *et al.*, 2017). From Piaget’s theory, we know that motor skill development in early childhood enables children to perceive the world, gain self-knowledge, and interact with others, which further facilitates improvement in other developmental domains (Goodway *et al.*, 2011). Thelen (1992) also stated that motor skills develop interactively with perceptual, social, and cognitive abilities. However, some evidence indicates that once children enter kindergarten, this interactive relationship seems reduce or become limited to specific domains (Hagmann-von Arx *et al.*, 2016; Kenny *et al.*, 2016; Libertus and Hauf, 2017; Cadoret *et al.*, 2018). While, little is known about the relationship between preschoolers’ motor skills and the development of other critical domains (such as physical fitness, and socioemotional and cognitive skills). Stodden *et al.* (2008) suggested that physical activity and motor skill competence might promote each other in early childhood. Furthermore, some systematic reviews have shown evidence that higher physical activity is associated with improved physical and psychosocial health indicators in preschool (Timmons *et al.*, 2012; Carson *et al.*, 2016, 2017).

Currently, in the area of health care, intervention projects designed to prompt physical activity and prevent obesity in children share three characteristics: 1) preschoolers are targeted; 2) children are provided with structured interventions carried out by teachers and experts, mostly in kindergartens or other child-centric contexts (Logan *et al.*, 2012; Van Capelle *et al.*, 2017; Hesketh *et al.*, 2017); and 3) they focus on fundamental movement skills (FMS) development, especially objective control skill interventions, like the CHAMP project (Robinson *et al.*, 2017; Veldman *et al.*, 2017; Palmer *et al.*, 2019), the Head Start curriculum (Robinson and Goodway, 2009), the SKIP project (Mulvey *et al.*, 2018; Taunton *et al.*, 2018), and other structured skill classes implemented by physical education (PE) teachers (Wadsworth *et al.*, 2020) or non-experts (Palmer *et al.*, 2020).

Learning and developing FMS competence, as supported by theoretical motor development models, is critical in preschool-age children. FMS is considered the building block of more complex and advanced skills, which means that mastering these abilities makes it easier for children to learn more specialized skills later on (Seefeldt *et al.*, 1980; Clark and Metcalf, 2002; Gallahue and Donnelly, 2007).

FMS terms such as “motor performance,” “motor proficiency,” “motor ability,” and “motor coordination” (Cattuzzo *et al.*, 2017) are often used interchangeably and inconsistently within the literature. In our study, we used the FMS definition: “basic learned movement patterns that do not occur naturally and are suggested to be foundational for more complex physical and sporting activities” (Barnett, Stodden, *et al.*, 2016). Thus, FMS includes locomotor (e.g., run, hop, slide), object control (e.g., dribble, throw, kick, also known as manipulative or ball skills) (Okely *et al.*, 2001), and stability skills (e.g., beam walk and one-foot balance) (Goodway *et al.*, 2011).

Evidence suggests that FMS has a positive association with multiple aspects of health in children, such as their physical activity levels, cardiorespiratory fitness, muscular strength and endurance, and healthy weight maintenance (Stodden *et al.*, 2008; Lubans *et al.*, 2010; Robinson *et al.*, 2015; Cattuzzo *et al.*, 2017), which are the foundations for the health and well-being of children. Studies have explored the association between FMS and variables of children in kindergartens, namely, social-emotional behaviors (Piek *et al.*, 2008; Robinson *et al.*, 2016; Ma *et al.*, 2019) and cognitive and academic performance (Planinsec, 2002; Niederer *et al.*, 2011; van der Fels *et al.*, 2015; Fang *et al.*, 2017; Cadoret *et al.*, 2018; Michel *et al.*, 2019).

In most countries, however, FMS competence is insufficiently developed in preschoolers (Taggart and Keegan, 1997; Hardy *et al.*, 2010; Robinson *et al.*, 2017), with this deficit continuing into primary school (van Beurden *et al.*, 2002; Hardy *et al.*, 2012; Spessato *et al.*, 2013; Mukherjee *et al.*, 2017; Wu *et al.*, 2017). Recently, a systematic review (Bolger *et al.*, 2020) of studies in typically developing children (3–10 years) worldwide demonstrated that FMS levels were “below average” to “average” according to the Test of Gross Motor Development-2 and that ball skills proficiency was less than locomotor skill. It was, therefore, recommended that in order to address these limitations, FMS interventions should be taught, practiced, and reinforced to children (Robinson and Goodway, 2009).

To date, multiple intervention projects have been implemented, but their effectiveness in healthy preschoolers remains controversial. There are many issues around this topic. First, some interventions lack a rigorous design and only record the outcomes directly after the intervention, with a lack of medium- and long-term follow-up (Wick *et al.*, 2017). Second, some interventions have limited assessment variables and focus narrowly either on a certain aspect of children’s health or risk development. Third, differential outcomes are often ignored in intragroup cases. Finally, there is a general lack of exploration of the social-ecological factors correlating with FMS competence (Barnett *et al*., 2016). It can be argued that FMS intervention projects should evaluate the interconnection of motor skill development with physical fitness, cognitive, and social abilities (subject to physical and environmental constraints), as these are the main aspects determining preschoolers’ health (Westendorp *et al.*, 2014; Leonard, 2016; True *et al.*, 2017; Zeng *et al.*, 2019).

### Background

In recent years, the Chinese government has promulgated policies to promote the development of basketball (Hu fengshen, 2017) and football (Ministry of Education of the People’s Republic of China, 2019) in kindergartens in order to develop students’ physique and talents. Although there is a rise in sport-centric characteristics among kindergarteners, and some successful examples, the question of how to use ball activities to promote early childhood development still needs exploration, along with a scientifically comprehensive evaluation of children’s developmental benefits resulting from participation in these games.

Based on the current cultural context and the potential importance of children’s ball skills for the long-term promotion and maintenance of health-related fitness (Stodden *et al.*, 2014), our research will use ball activities to promote FMS, cognitive performance, social skills development, and other health benefits. The “Hello Sunshine” (HS) project is a PE intervention project for preschoolers that uses various ball activities (football, basketball, badminton, table tennis, baseball, golf, handball, bowling, and snooker) as a strategy to promote multiple aspects of children‘s development. The HS project not only teaches football and basketball but also guides children to learn and experience different ball skills and have more fun with a variety of tasks and environmental constraints. It is likely that not every child will enjoy ball games and this gives us an opportunity to explore how social-ecological factors may influence intervention outcomes. It is hoped that this study will provide a basis for a pedagogical method to improve preschooler’s ball skills.

### Theoretical framework

It is well known that theories and models used in the health promotion and educational fields provide a framework for developing, understanding, and carrying out interventions (Glanz *et al.*, 2008). Our theoretical framework, including its concepts, models, and theories, is described below (Figure 1).

**Figure 1. f1:**
[figure not shown]
Theoretical framework of this project

Our theoretical framework utilized Bronfenbrenner’s ecological systems theory (Bronfenbrenner, 1979) and Stokols’ social ecology model for health promotion (Stokols, 1992) to guide the targeting of specific factors when designing this intervention project and explaining its outcomes. According to the proposed model, children’s behavior is influenced by the individual, their affiliations to people, organizations, and the community, and at the public policy level, and these are collectively known as social-ecological factors. Cool *et al.* (2011) identified that parental education, father’s physical activity, and parental rearing pattern had a relationship with preschooler’s FMS performance. In a meta-analysis, Barnett *et al*. (2016) found that FMS competence was correlated with individual factors, such as age, healthy, weight, range, sex (male), and family socioeconomic status (higher). Zeng *et al.* (2019) suggested the different components of a preschooler’s FMS have multidimensional relationships with social-ecological factors at the child, family, and environmental levels, and Niemistö *et al.* (2020) considered individual factors (age, physical, and specific temperament) to be the most important predictors of FMS.

Teachers and teaching strategies at the kindergarten level are hypothesized to be important factors when initiating children’s FMS programs. At this point, multiple human–environment interactions take place, which, in addition to children’s characteristics, influence their FMS levels and the effects of interventions.

Our intervention project will be based on the concept of cultivating physically literate individuals. Physical literacy was first proposed by Whitehead (2013) and has now become globally accepted as a key element in quality PE, according to the United Nations Educational, Cultural, and Scientific Organization (McLennan and Thompson, 2015). The ball skills teaching method is game-based and pursues the interaction of different constraints – task, environment, and performer (Newell 1986).

The outcomes of this project will allow us to explore the effects of this intervention on the physical, motor, cognitive, and social development of preschoolers, according to the motor development process and dynamic systems theory (Thelen, 1992), as well as the relationship among physical activity, FMS perceived competence, and health-related fitness as Stodden’s model (Stodden *et al.*, 2008). Additionally, based on existing studies, we used the social-ecological model to explain individual differences in the intervention’s outcomes (Glanz *et al.*, 2008; Bellows *et al.*, 2013; Taunton *et al.*, 2018; Zeng *et al.*, 2019).

## Materials and methods

The study protocol complies with the guidelines of the SPIRIT 2013 statement (Chan *et al.*, 2013). The trial was registered with the Chinese Clinical Trial Registry (registration number: ChiCTR2000035414) on 10 August 2020 and will be carried out in accordance with the Declaration of Helsinki.

Children, aged 4–6 years, from three predetermined kindergartens will participate. The three kindergartens are categorized based on three different PE programs provided for the children: a Hello Sunshine (HS), an ordinary PE (OPE), and a free play (FP) depending on their existing PE curriculum.

### Aim

This study aims to conduct a “Hello Sunshine” curriculum project and evaluate its effects on the development of physical, motor, cognitive, and social competence in preschoolers. It also aims to determine the social-ecological factors influencing the intervention’s effect.

### Objectives

To assess the effects of the HS project on the development of children’s physical (anthropometric, physical fitness), motor (FMS), cognitive (perception, self-regulation), and social (emotional comprehension) development and to contrast intervention effects between different PE course groups.To use a social-ecological perspective to explore the factors affecting different intragroup outcomes in the intervention groups.To identify the main factors impacting the efficiency of the HS intervention at an intragroup level.

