### Research questions

The following research questions are proposed in this study:What are the effects of the HS project interventions on the physical fitness and motor development of preschool children, as well as on their cognitive and social competencies?How do intervention effects differ among the HS group, the OPE group, and the FP group?To what extent are the intervention gains on the HS groups mediated by personal factors?What are the main social-ecological variables related to differences in the intervention outcomes?To what extent are the outcome variables related to each other?

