### Hypotheses

Based on these five research questions, we hypothesize that children in all groups will exhibit improvements in developmental outcomes across the 10-week period. We predict participants in the HS groups will report significantly higher scores on physical fitness, FMS, and cognitive self-regulation tests at follow-up, compared to baseline. We also expect improvements in these indicators to be significantly greater when compared to the alternative programs (OPE and FP).We also hypothesize that differential intervention effects within the HS groups will be associated with the individual, family, and environmental factors.

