## Results

Data will be imported from Excel 2019 to IBM SPSS version 26.0 for inferential statistical analysis. The normal distribution of the data will be checked before determining the descriptive statistics for all variables (means and standard deviations). The participants’ basic information will be descriptive, including age, gender, and BMI. The primary outcomes will be expressed as continuous. If data are approximately normal distribution, the effect of the PE curriculum intervention on dependent variable (FMS, or TGMD, or HTKS, or SCEB score) will be investigated with repeated ANOVAs within factor: time (pre and post), between factors: group (HS, OPE, and FP) and gender (boy and female) and Bonferroni post hoc tests. Further, the relationship between FMS and other domains will be identified by regression analysis. Finally, the potential influence of individual factors (such as age, gender, and temperament) on the intervention effect will be investigated by comparing the gain in FMS score and subscale. Multiple regression equation is used to further explore the extent to which social-ecological factors contribute to the FMS score level at baseline. Statistical significance will be set at *P* < 0.05.

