### Strengths and limitations

One of the strengths of this project is that the quasi-experimental study comparing three parallel groups of PE in kindergartens using blinded assessors. This study design is implemented in realistic environment where the kindergartens are likely to be more cooperative as they can keep their existing curriculum arrangements. The HS group is mainly focused on ball skills, the other two teaching methods represent the mainstream PE activities employed in most kindergartens; the OPE group covers multiple types of physical activity taught by PE teachers, and the control group’s main characteristic is FP. Our research will involve a comprehensive quantitative analysis of the immediate and follow-up effects of the interventions on four domains of children’s development and will collect information from multiple informants including from children, their parents, and their teachers. Finally, the impact of social-ecological factors on the interventions’ effects will be analyzed.

A limitation of this research will be the large number of items tested in this project, as these will take more time to collect and may stress the children’s patience levels. The short forms of each of the established tests have been selected. Exercise interventions in outdoor environments are also affected by weather conditions, including rain, and/or overheating during high temperatures, and the effects of the COVID-19 pandemic. Such factors may affect both delivery and compliance. Further randomized controlled trial studies conducted in more kindergartens will broaden our understanding of the impact of ball skills learning on children’s development, and a cohort study will be established to explore the long-term effects of ball skill learning on children.

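### The aims ask what drives response to HS across all outcomes, but apart from gender the planned factor analyses use FMS only, and family and environmental factors are related to gain in no domain

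*Protocol article*

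**What the plan says.** The aims come first. Objective 2 is to "explore the factors affecting different intragroup outcomes in the intervention groups". Objective 3 reads "To identify the main factors impacting the efficiency of the HS intervention at an intragroup level". Research question 3 asks "To what extent are the intervention gains on the HS groups mediated by personal factors", and research question 4 asks "What are the main social-ecological variables related to differences in the intervention outcomes". The last hypothesis expects that "differential intervention effects within the HS groups will be associated with the individual, family, and environmental factors". None of these names FMS or any other single outcome. Objective 1 and Table 1 (Outcome measures) set out what the outcomes are: physical, motor, cognitive and social development, all in the primary block. Strengths and limitations likewise speaks of "effects of the interventions on four domains of children’s development" and then promises an analysis of how social-ecological factors affect the interventions' effects.

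The analyses are in the Results section. The influence of individual factors (age, gender and temperament are given as examples) on the intervention effect "will be investigated by comparing the gain in FMS score and subscale". A multiple regression then explores "the extent to which social-ecological factors contribute to the FMS score level at baseline". The same section plans a repeated ANOVA of time, group and gender, with FMS or TGMD, HTKS and SCEB as dependent variables, and a regression relating FMS to the other domains.

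**The concern.** The question is general and the analysis meant to answer it is narrow. Age, temperament or family background could relate to gain in motor skill in one way and to gain in self-regulation, social competence or fitness in another. An FMS analysis cannot settle that for the other domains.

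The social-ecological regression has a further limit. Its outcome is FMS before the intervention starts, so it describes who begins with better skills. It does not show who responds to HS, even in the motor domain.

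The protocol's own rationale makes this matter. The Introduction criticises earlier work for narrow assessment and for ignoring differences in response within groups. The Abstract says the social-ecological findings should help to improve teaching methods. A statement about who benefits from HS would have support for part of one domain only.

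**Working it through.** No sample size, power or alpha figure is involved, so there is nothing to recalculate. The check sets the aims beside the analyses.

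**Step 1: scope of the aims.** Objectives 2 and 3, research questions 3 and 4 and the last hypothesis refer to outcomes, gains, efficiency or effects without restriction. With objective 1 and Table 1, that means four primary domains.

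**Step 2: outcome of each planned analysis (Results section).**
- Individual factors: gain in FMS, total and subscale.
- Social-ecological factors: FMS level at baseline.
- Repeated ANOVA: FMS/TGMD, HTKS and SCEB, with group and gender as between factors. No fitness or anthropometric measure is named.
- Regression of FMS with the other domains: this relates outcomes to each other and so answers research question 5. It does not examine factors behind response.

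**Step 3: cross-tabulation of factors against change, by primary domain.**

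| Domain (measure) | Gender | Age, temperament | Family, environment |
|---|---|---|---|
| Motor (TGMD-3) | yes: gain comparison and ANOVA | yes: gain comparison | no: baseline level only |
| Cognitive (HTKS) | yes: ANOVA | no | no |
| Social (SCEB-30) | yes: ANOVA | no | no |
| Physical (anthropometrics, fitness) | none named | no | no |

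**Step 4: count.** Gender is covered for 3 of 4 domains, age and temperament for 1 of 4, and family and environmental factors for 0 of 4.

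**Step 5: does the ANOVA close the gap?** No. It spans all three groups and is not described as an analysis within HS, whereas the objectives and the hypothesis concern differences within the intervention group. It also contains no factor other than gender.

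**The case against.** Four arguments on the other side deserve weight.

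- **The FMS focus fits the background.** The Introduction names the gap as too little work on social-ecological correlates of FMS. The Theoretical framework reviews determinants of FMS, and the covariate section justifies temperament and physical activity by their link to motor skills. An FMS-only intention is plausible. If that is the intention, the aims are worded too broadly, which still needs correcting.
- **The hypothesis may be narrower than four domains.** The preceding prediction of an HS advantage covers fitness, FMS and self-regulation, and not SCEB-30. If the last hypothesis is read against those three indicators, it leaves two domains without an analysis of age and temperament, not three. The objectives and research questions carry no such limit.
- **The aims are secondary and partly exploratory.** This is fair, and it keeps the remedy modest.
- **An article may leave further models to a fuller document.** That would excuse silence, but the Results section is not silent. It lists several outcomes for the group comparison and names FMS alone for the factor analyses.

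A reader might infer more than the document supports:
- It is not true that three primary domains go unanalysed. HTKS and SCEB have the time-by-group ANOVA.
- It is not true that every factor analysis is confined to FMS, because gender enters that ANOVA.
- A count by individual measure in Table 1 would make the gap look larger, but only because height, weight and each fitness test would count separately.
- The article nowhere says that FMS factor results will be presented as conclusions about the other domains. That is a risk left open by the wording of the aims.

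**Conclusion.** The concern holds in a limited form. Objectives 2 and 3, research questions 3 and 4 and the last hypothesis ask about response to HS in general, while the two analyses assigned to them fix FMS as the outcome. This is a mismatch within the document. Age and temperament are examined against gain in one of four primary domains, and family and environmental factors against gain in none, the motor domain included. Gender in a three-group ANOVA is a partial exception that does not supply the missing analyses.

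The conclusion takes the Results section as written. If a fitness score was meant among the ANOVA outcomes, gender would be covered in the physical domain too, and the counts for the other factors would not change. The planned group comparisons are not affected by this point.

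**What to change.** Choose one of two routes and word the aims and the Results section to match.

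1. **Keep the general aims.** Within the HS group, add models of pre-to-post change in FMS, fitness, HTKS and the SCEB-30 subscales on the individual, family and environmental factors already being collected. Adjust each for the baseline value of its outcome and label the set exploratory. The existing social-ecological regression cannot simply be repeated for other outcomes, because it models a baseline level; the change models have to be written out.
2. **Narrow the aims.** Restrict objectives 2 and 3, research questions 3 and 4 and the last hypothesis to FMS gain. Model the social-ecological factors on FMS gain and not only on baseline FMS. State that no conclusion on response factors will be drawn for fitness, self-regulation or social competence.

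Neither route needs new data. The first adds exploratory tests in a group planned at 83 children, so its results should be read as descriptive. The second gives up part of the claim. Narrowing the wording without changing the baseline regression would still leave research question 4 and the family and environmental part of the hypothesis unanswered.
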